**Sample size calculation:**

Sample size (n=120) is calculated using G\*Power based on the effects on pain in a pilot study (Cohen's  $f = 0.25$ ,  $\alpha = .05$ ,  $\text{power} = .80$ ), accounted for F-tests and 20% loss to follow-up after one year.

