**Randomisation:**

Randomization is computer-generated at the Biostatistics Unit of Ghent University by an independent investigator, uninvolved in any other trial aspects. Block randomisation was used (ratio 1:1) for the two treatment centres (Ghent; Brussels) separately, with stratification for sex (male; female) and dominant pain location (neck; low back). The randomisation is performed by an independent researcher, who places papers indicating group assignment in sequentially numbered, opaque, and sealed envelopes. Concealed allocation is ensured since the independent researcher – who will be the only person with access to the envelopes – writes the initials of the selected participants on the appropriate envelope before opening them.

**Outcome measures:**Primary outcome:

The primary clinical outcome is defined as average pain intensity, assessed using the Brief Pain Inventory (BPI) item 'average pain intensity in the last 24h' evaluated on an 11-point NRS (30% decrease is clinically important).

Explorative, secondary pain-related outcomes:

- BPI worst pain intensity (last 24h) on an 11-point (0–10) numeric rating scale
- BPI least pain intensity (last 24h) on an 11-point (0–10) numeric rating scale
- BPI pain intensity now on an 11-point (0–10) numeric rating scale
- BPI pain severity: the mean of the four pain intensity items
- BPI pain interference: the BPI also evaluates the pain interference related to general activity, walking, work, mood, enjoyment of life, relation with others and sleep on separate 11-point numeric rating scales.
- The Central Sensitisation Inventory (CSI; cut-off value of 40/100 to indicate the presence of central sensitization-related symptoms) to assess symptoms of central sensitisation. The CSI uses 25 statements related to current health symptoms, indicative of central sensitization (scored on a five-point Likert scale ranging from zero to four).

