- Pressure pain thresholds (PPT; increase of >15% is clinically important), defined as the point of minimum pressure that induces an unpleasant sensation is assessed with a digital pressure algometer (Wagner instruments), randomly applied at the painful and two remote locations. The painful level is the trapezius muscle in neck pain patients and at L3 lumbar paravertebral muscles in low back pain patients. Remote sites are the web between the thumb and the index and the proximal one third of the calf. The threshold is determined as the mean of two consecutive measurements, with 30 s in between.

Explorative, secondary sleep-related outcomes:

- The Pittsburgh Sleep Quality Index (cut-off = 6/21; 3 points difference as clinically important) to assess self-reported perceived sleep quality. It is a 19 item scale with 1 week time interval. Its score ranges between 0 and 21 and 0 indicates no sleep difficulty and 21 indicating severe sleep difficulties.
- The Insomnia Severity Index (cut-off = 14/28; 6 points difference as clinically important) to assess self-reported insomnia severity. It is a 5-item 5-point Likert scale applying a 2 week time interval. Its scores range between 0 and 28 and 0 indicates no clinically significant insomnia and 28 indicating severe clinical insomnia.
- Dysfunctional Beliefs and Attitudes about Sleep questionnaire to assess self-reported dysfunctional beliefs and attitudes about sleep. It is a 16-item 5-point Likert scale with scores ranging between 0 and 10. Scores over 4 indicate unrealistic expectations for sleep or unrealistic thoughts about sleep.
- The Epworth Sleepiness Scale to assess self-reported sleep propensity. It is an 8-item 4-point Likert scale, with scores ranging between 0 and 24 and with 0 indicating normal daytime sleepiness and 24 indicating severe excessive daytime sleepiness.
- The Brugmann Fatigue Scale to assess self-reported fatigue severity with mental fatigue subscale and physical fatigue subscale. The score ranges from 0 to 24 and higher scores indicate a higher subjective level of fatigue.

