### Statistical analysis plan

1. **Data source:** Data are derived from nCSP patients with insomnia who participate in this randomised controlled trial. They were evaluated at baseline, at post-intervention and at 3, 6 and 12 months follow-up. The primary outcome is average pain intensity in the last 24h assessed with the BPI.
2. **Analysis objectives:** To investigate the effectiveness of CBTi-BEPM versus BEPM in terms of the above-mentioned primary outcome at 12 months follow-up, and pain-related, sleep related and other secondary exploratory outcomes.
3. **Population:** nCSP patients with insomnia
4. **Endpoints:** Change in outcome measures from baseline to each follow-up point
5. **Covariates:** Sensitivity analyses performed for the primary outcome and all exploratory outcomes by controlling for baseline levels of pain intensity for pain-related outcomes and baseline levels of insomnia severity for sleep-related outcomes. These baseline levels were added to the random-intercept fixed slope linear mixed model analysis as confounding factor.
6. **Handling of missing data:** Analyses are carried out using linear mixed models which can handle missing data.
7. **Statistical methodology:**  

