Descriptive statistics were used to report the demographic variables and baseline characteristics of the participating nCSP patients per intervention group, with means (Standard Deviation [SD], range and Inter Quartile Range [IQR]) for continuous variables and frequency (%) for categorical variables. All analyses were by intention-to-treat, with all participants included in the analysis according to their randomly allocated treatment. All analyses were performed in SPSS 24.0. For average pain intensity (primary outcome) and for all explorative, secondary outcomes, the change between baseline and other time points was calculated:  $\Delta 1 = \text{baseline (T0)} - \text{post-treatment (T1)}$ ;  $\Delta 2 = \text{T0} - \text{3-month follow-up (T2)}$ ;  $\Delta 3 = \text{T0} - \text{6-month follow-up (T3)}$ ; and  $\Delta 4 = \text{T0} - \text{12-month follow-up (T4)}$ . Differences in the change in average pain intensity at 12-month follow-up (primary outcome at primary endpoint) and at the other time points (immediately post-intervention, and at 3- and 6-month follow-up) were analysed using a random-intercept fixed slope linear mixed model (incl. LSD post-hoc analyses), which was applied using an unstructured covariance matrix. Linear mixed models are a likelihood-based estimation procedure whereby likely values for missing data are estimated from information contained in the observed data, resulting in non-biased estimates providing data are missing at random. The model included treatment, time, and treatment\*time as fixed effects together with a random intercept for each patient. Model assumptions were evaluated visually using residual plots. Mean group differences (95% confidence interval) at the different time points and their p-values and effect sizes for the intervention comparisons are reported. Level of significance for the primary outcome was set at  $\alpha .05$ . Effect sizes were calculated as Cohen's d (interpreted as  $>1.3$  = very large;  $.80-1.29$  = large,  $.50-.79$  = medium,  $.20-.49$  = small,  $<.20$

= negligible). The same analysis was used to evaluate the explorative, secondary outcomes at the different time points.

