Sensitivity analyses were performed using the same analysis, including the baseline level of average pain intensity (for all pain-related outcomes) and the baseline level of insomnia severity (for sleep-related outcomes) as confounding factor. The analysis of dropout and loss-to-follow-up was conducted by categorizing the entire cohort into two subsets, distinguished by their adherence or discontinuation from the trial (which also included loss-to-follow-up). Comparative assessment of baseline characteristics and data between the two groups was accomplished utilizing a t-test or its non-parametric equivalent.

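### Centre, sex and dominant pain location define the randomisation strata but appear in no model; to the extent that they predict change in pain, the planned intervals are somewhat too wide and the test is conservative

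*Combined protocol and SAP*

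**What the plan says.** The Randomisation section of the protocol states: "Block randomisation was used (ratio 1:1) for the two treatment centres (Ghent; Brussels) separately, with stratification for sex (male; female) and dominant pain location" (neck or low back). I read this as 2 × 2 × 2 = 8 strata. Block size is not stated.

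Item 7 (Statistical methodology) of the Statistical analysis plan lists the terms of the primary model in full: treatment, time and treatment-by-time "as fixed effects together with a random intercept for each patient". The same analysis is used for every secondary outcome. The endpoint is change from baseline, and 12 months is the primary time point.

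Item 5 (Covariates) confines adjustment to sensitivity analyses, "controlling for baseline levels of pain intensity for pain-related outcomes and baseline levels of insomnia severity for sleep-related outcomes". The last part of item 7 repeats this. No analysis in the plan contains centre, sex or pain location, and no reason for leaving them out is given.

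**The concern.** The design and the analysis do not match. Stratified blocking keeps the arms close to balanced on the three factors, so differences between centres, sexes and pain locations contribute little to the true sampling error of the treatment difference. If the model has no terms for them, that variation stays in the residual variance. The reported standard error is then larger than it should be, the confidence interval is too wide, and the test rejects less often than its nominal level.

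What is at stake is precision already paid for in the randomisation. Naming the model terms in advance also removes any later choice between adjusted and unadjusted results.

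**Working it through.** **Inputs from the documents.** The Sample size calculation section gives n = 120, Cohen's f = 0.25, α = .05, power .80 and 20% loss at one year. For two equal arms f = 0.25 means d = 0.5. Patients analysed: 120 × 0.80 = 96, or 48 per arm. Sidedness is not stated; I take α as two-sided, as an F-test between two arms implies.

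**The plan's own figure.** A plain two-group F-test with f = 0.25 needs 128 evaluable patients, and 128/0.80 = 160, not 120. A repeated-measures between-groups F-test with two measurements and correlation 0.5 needs 98, which becomes 123 (98/0.80) or 118 (98 × 1.20). Three measurements with correlation 0.6 need 96, and 96/0.80 = 120. So 120 can be reproduced, but only with settings that the protocol does not state.

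**Assumption.** R², the share of the variance of 12-month change explained by the three factors together, is not in the documents. I use 0, 0.05, 0.10 and 0.20.

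**Formulas** (outcome SD = 1, complete balance, normal approximation):

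- Standard error reported without the factors: s = √(4/96) = 0.204. True standard error under balance, which the adjusted model also reports: s√(1 − R²).
- Interval width, unadjusted over adjusted: 1/√(1 − R²).
- Type I error of the unadjusted test: 2[1 − Φ(1.96/√(1 − R²))].
- Power, unadjusted: Φ((d − 1.96s)/(s√(1 − R²))). Power, adjusted: Φ(d/(s√(1 − R²)) − 1.96).

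Example, R² = 0.10: the true standard error is 0.204 × 0.949 = 0.194. The width ratio is 1/0.949 = 1.05. Unadjusted power is Φ((0.5 − 0.400)/0.194) = 69.7%; adjusted power is Φ(0.5/0.194 − 1.96) = 73.3%.

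**Simulation.** Loss to follow-up disturbs the balance, so the formulas were checked by simulation: 120 patients, 8 strata, permuted blocks of 4 (assumed), 20% loss at random, 8000 runs per setting, and a linear model of 12-month change with and without the factors. The Monte Carlo standard error of a 5% rate is √(0.05 × 0.95/8000), about 0.2 points. Type I error was simulated more than once for R² above 0, and the range is shown.

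| Assumed R² | Width ratio | Type I, complete balance | Type I, simulated, 20% loss | Power without → with factors, formula | Same, simulated, 20% loss |
|---|---|---|---|---|---|
| 0 | 1.00 | 5.0% | 5.0% | 68.8 → 68.8% | 67.2 → 66.9% |
| 0.05 | 1.03 | 4.4% | 4.5–4.9% | 69.2 → 71.0% | 69.0 → 70.3% |
| 0.10 | 1.05 | 3.9% | 4.0–4.4% | 69.7 → 73.3% | 68.1 → 71.4% |
| 0.20 | 1.12 | 2.8% | 3.3–3.5% | 70.8 → 78.2% | 69.5 → 76.9% |

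**Where the loss arises.** With no loss to follow-up and R² = 0.10, the unadjusted model reported a mean standard error of 0.182 against a true 0.172, with type I error 3.8%. The adjusted model reported 0.173 against 0.172, with type I error 4.9%. The two estimators are almost equally precise, so the fault lies mainly in the reported standard error.

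**Which terms are needed.** Item 7 defines change scores but does not make clear whether these or the raw scores including T0 are the model's responses. If T0 is a response, a time-constant factor effect γ enters both the T0 and the T4 score and cancels from T0 − T4. Main effects alone then leave the change contrast essentially as it was.

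**The case against.** The best reply is that the loss is conditional and small. It exists only if the factors predict change in pain, not merely its level, and nothing in the documents says that they do. Subtracting baseline already removes stable differences between centres, sexes and locations. The error is on the safe side. All of this stands, and it limits the point to a modest one. It is not a reason to omit the factors: at R² = 0 adjustment costs next to nothing (67.2% against 66.9% in simulation, within Monte Carlo error).

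Item 7 also describes the analyses largely in the past tense. If they have already been run, an adjusted model can only be a supporting analysis. That stands too.

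Three stronger readings are tempting, and the documents do not support them:

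- *The omission is worse for the painful-site pressure threshold.* The Outcome measures section does pool two sites: "The painful level is the trapezius muscle in neck pain patients and at L3 lumbar paravertebral muscles in low back pain patients". But the analysis is of change, and a constant difference between muscles cancels from each patient's change. Only a difference in change by site would matter, and no figure bears on that.
- *The trial is already short of its stated power.* The protocol plans power .80. The values near 68% above belong to a plain two-group comparison at one time point. Because the test family behind n = 120 is not stated, they do not show a shortfall.
- *The type I error falls to 2.8%.* That needs R² = 0.20 and complete balance among those analysed. With the expected 20% loss it is 3.3 to 3.5%.

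**Conclusion.** The mismatch between randomisation and analysis is plain from the text; its size is not known. For an assumed R² of 0.05 to 0.10, the planned intervals are about 3 to 5% wider than those of a model with the factors. The type I error is about 4.0 to 4.5% (one simulated value of 4.9% at R² = 0.05 lies within Monte Carlo error of this), and about 1 to 4 power points are lost. At R² = 0.20 the figures are about 12%, 3.3 to 3.5% and 7 to 8 points. At R² = 0 there is no loss.

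These figures rest on d = 0.5, 96 patients analysed, two-sided α = .05, blocks of 4 and loss unrelated to the factors. A reader might infer that the primary result would be biased or the test invalid. Neither follows: the omission does not shift the estimate, and it makes the test conservative. The change is worth making because it costs so little, not because the conclusion is in danger.

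**What to change.** State in items 5 and 7 of the Statistical analysis plan that centre, sex and dominant pain location are fixed effects in the primary model and in all secondary models, or give a reason for leaving them out. In the same sentence, say which responses the model uses:

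- If change scores, the three main effects are the minimum: 3 parameters, which takes about 94 residual degrees of freedom (96 − 2) to 91.
- If raw scores including T0, add each factor's interaction with time. With five time points that is 3 + 3 × 4 = 15 parameters, and fewer for outcomes not measured at 3 and 6 months.

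The cost is one or two sentences and a few degrees of freedom. All three factors are known at randomisation, so no new data are needed. If the analysis has already been run, report the adjusted model beside the planned one and label it as added afterwards.

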#### Explorative, secondary other outcomes:

- The Hospital Anxiety and Depression rating scale (HADS) to assess self-reported affective symptoms. It is a 14-item scale with depression subscale and anxiety subscale. Score ranges from 0 to 21, with 0 indicating absence of depression or anxiety and 21 indicating the presence of depression or anxiety. It includes a 7-item 4-point Likert 'depressive symptoms' subscale (0-21) and 7-item 4-point Likert 'Anxiety' subscale (0-21). Both apply a 4 week time interval
- The Short Form Health Survey-36 (SF-36) to assess physical and mental functioning. The SF-36 is widely used a generic measure of health-related quality of life and constitutes well characterised psychometric properties.
- Physical activity recorded over 7 consecutive days by three-axis wrist worn accelerometers (GT9X-BT, Actigraph) will be used to define number of steps and percentage in level of activity (sedentary, light, moderate, vigorous) will be used as measure of physical activity.
- Adverse events classified as serious (led to death, life-threatening, required hospitalization, prolonged hospitalization, led to prolonged or significant disability).

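### For most secondary outcomes no model adjusts for the outcome's own baseline; the sensitivity covariate is chosen by outcome family and is not named for HADS, SF-36 or physical activity

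*Combined protocol and SAP*

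**What the plan says.** Under SAP item 7 (Statistical methodology), each outcome is turned into a change, baseline (T0) minus each later visit. The changes are analysed in a mixed model with arm, visit and their interaction as fixed effects and a random patient intercept. The secondary outcomes use the same model. It contains no baseline covariate.

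Baseline covariates appear only in the sensitivity analyses. SAP item 5 (Covariates) controls pain-related outcomes for baseline pain intensity and sleep-related outcomes for "baseline levels of insomnia severity for sleep-related outcomes". The closing paragraph of item 7 repeats the rule: baseline average pain for the pain family, and "the baseline level of insomnia severity (for sleep-related outcomes) as confounding factor". Item 5 says that these analyses cover the primary outcome and every exploratory outcome.

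Set against the protocol's outcome lists, the rule works out as follows:

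| Outcome | Baseline covariate in the sensitivity model | Own baseline? |
|---|---|---|
| Average pain (primary) | average pain | yes |
| BPI pain severity | average pain, one of its four items | in part |
| BPI worst, least and current pain; BPI interference; CSI; pressure pain thresholds | average pain | no |
| Insomnia Severity Index | insomnia severity | yes |
| PSQI, DBAS, Epworth, Brugmann fatigue, polysomnography | insomnia severity | no |
| HADS, SF-36, physical activity | none named | no |

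**The concern.** Subtracting the baseline is not the same as adjusting for it. When r is below 1, patients with a high T0 value tend to fall and those with a low one tend to rise. If chance gives one arm the higher T0 mean, part of that difference appears as a difference in change. The variable that governs this is the outcome's own T0 value, and most secondary outcomes do not get it as a covariate in either model.

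The plan calls its covariates confounding factors, so a reader will take a sensitivity result that barely moves as evidence that baseline differences do not matter. For a pressure pain threshold or total sleep time, that result says little about imbalance in the threshold or the sleep time itself. Precision is also given up. For HADS, SF-36 and physical activity the promised sensitivity analysis cannot be run as written, because no covariate is specified.

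**Working it through.** **Inputs from the documents.** 120 patients at 1:1, so 60 per arm. The sample size is "accounted for F-tests and 20% loss to follow-up after one year", which leaves 120 × 0.8 = 96 patients, or 48 per arm. The plan gives no figure for baseline adjustment, so there is none to reproduce on this point. Its one planning figure, 120, is "based on the effects on pain in a pilot study". It is approximately recovered by a repeated-measures F-test of the between-group effect with two measurements and a correlation of 0.5, neither of which is stated: 98 completers, and 98/0.8 = 122.5, so 123. A plain two-group F-test gives 128, and 128/0.8 = 160. Nothing below depends on this.

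**Assumptions.** The outcome has SD 1 at baseline and follow-up, and one visit is compared at a time. r is the correlation of own baseline with follow-up (0.3, 0.5, 0.7). r0 and r1 are the correlations of the other baseline with the outcome's baseline and with its follow-up (r0 from 0.2 to 0.7).

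**1. Imbalance left in the change score.** An own-baseline difference d between arms shifts the expected difference in change by d(1 − r). A one-SE difference at 60 per arm is √(2/60) = 0.183 SD.
- r = 0.3: 0.7 × 0.183 = 0.13 SD
- r = 0.5: 0.5 × 0.183 = 0.09 SD
- r = 0.7: 0.3 × 0.183 = 0.05 SD

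Own-baseline adjustment removes this shift.

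**2. Precision from the own baseline.** The variance of the change is 2(1 − r). After own-baseline adjustment it is 1 − r². The reduction is (1 − r)/2, which is 35%, 25% and 15% at r = 0.3, 0.5 and 0.7.

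**3. The same for another variable's baseline.** The variance after adjustment is 2(1 − r) − (r0 − r1)². The share of the imbalance shift removed is r0(r0 − r1)/(1 − r).
- If r1 = r0, both benefits are zero.
- If the other baseline predicts follow-up only through the own baseline, r1 = r0 × r. The variance reduction becomes r0²(1 − r)/2 and the share of the shift removed becomes r0².

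For the second case at r = 0.5:

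| r0 | Variance reduction | Imbalance shift removed |
|---|---|---|
| 0.2 | 1.0% | 4% |
| 0.3 | 2.3% | 9% |
| 0.5 | 6.3% | 25% |
| 0.7 | 12.3% | 49% |
| own baseline | 25% | 100% |

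A simulation with 96 patients at r = 0.5 agrees: variance reductions of about 5% at r0 = 0.5, 11% at r0 = 0.7 and 25% with the own baseline.

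**4. In terms of power.** Take a true difference of 0.5 SD, 48 per arm, r = 0.5 and two-sided 0.05 (normal approximation). Power is 0.688 for the unadjusted change, 0.716 with another baseline at r0 = 0.5, and 0.807 with the own baseline. At r = 0.3 the unadjusted and own-baseline values are 0.544 and 0.728; at r = 0.7 they are 0.885 and 0.929.

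**The case against.** The strongest reply is that nothing here is invalid. A change-score contrast in a randomised trial is unbiased on average, and its confidence interval already allows for chance baseline variation. That stands: the loss is in precision and in the estimate conditional on an observed imbalance. The residual shift is also small. At 0.09 SD for a one-SE imbalance, it lies below the 0.20 that the SAP itself calls negligible.

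The outcomes are labelled exploratory, and the SAP sentence that begins "Level of significance for the primary outcome was set at" fixes an error level for the primary outcome alone. That stands too, and it limits the weight of the point.

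It can further be said that the covariates are meant to test robustness to clinical severity at entry, and that the SAP does not claim they deal with regression to the mean. That is a fair reading and a reason to allow them as extra covariates. It does not explain why the own baseline is left out, nor why HADS, SF-36 and physical activity have no covariate.

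A reader might infer that the stated adjustment does nothing for imbalance or precision. The documents do not support this. It is exactly true only if the covariate correlates equally with baseline and follow-up, and closely related measures, such as the other BPI intensity items with average pain, could gain appreciably. A reader might also infer that a baseline imbalance enters the treatment effect in full. It does not, because the change score has already subtracted the baseline.

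**Conclusion.** The point holds for most secondary outcomes, not all. The text alone establishes that the covariate is specific to the outcome family rather than to the outcome, and that item 5 promises an analysis which is undefined for three outcomes in the remaining family. The size of the loss rests on assumed correlations, equal SDs and single-visit comparisons. Under these it is a modest but real loss of precision and an incomplete correction of chance imbalance. It is not a bias in the trial's design. The primary outcome already receives its own baseline in the sensitivity analysis, so neither the primary conclusion nor the sample size is touched. This is an inexpensive improvement to exploratory analyses.

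**What to change.** Replace the family rule in SAP item 5 and in the last paragraph of item 7 with one sentence: for every secondary outcome with a T0 value, the mixed model for change includes that outcome's own T0 value as a covariate. For pressure pain thresholds, use the T0 value at the same site. The sentence should expressly include HADS, SF-36 and physical activity, and exclude adverse events, which have no T0 score. A baseline-by-visit term is optional. Baseline average pain and baseline insomnia severity can stay as additional sensitivity covariates.

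The cost is one sentence and one extra term per model. No new data are needed and no patient is lost, because a change score cannot be formed without the T0 value.
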